### Missing data

For missing data in this study, the percentage of missing data will be reported, the potential patterns of missing data should be examined, and appropriate method should be used for multiple imputation of missing data. The multiple imputation method will be preferred for analyzing the missing data, and the complete-case data should be reported in the manuscript as sensitivity analysis. The patients' demographic characteristics were involved in the missing data model for multiple imputation, and the number of multiple imputation will be set as 5.

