## 2、 Statistical Analysis Plan

### Data set

After the electronic database was locked, the database was divided into Intention-to-Treat analysis (ITT), Per Protocol analysis (PP), and Safety Set (SS) using the following criteria.

**Intention-to-treat (ITT)** refers to all participants who were randomized into different treatment groups, regardless of whether they completed the treatment as assigned or not.

**Per protocol (PP)** refers to the set of cases that meet the inclusion criteria, do not meet the exclusion criteria, and have completed the treatment protocol. Each subject in the PP dataset is a valid case or sample with good adherence, no protocol violations, and complete baseline values for key indicators. Prespecified sensitivity analyses were conducted using complete-case data.

**Safety set (SS)** refers to the actual data for subjects who receive at least one intervention after randomization and for whom safety indicators are documented. The incidence of adverse reactions is calculated using the number of cases in the safety set.

**Adverse events:** Will be analyzed, with the number of cases, category, and severity of occurrences counted separately and their relationship to the intervention.

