### Data management and general analysis

A comparison of baseline characteristics of the selected subjects in the two groups was conducted to assess comparability. Intervention effect evaluation included determining

intervention effect indicators and comparing intervention effects between groups. The primary outcome evaluation used the ITT dataset as the main dataset for intervention effect evaluation and the PP dataset for sensitivity analysis. Secondary outcome indicators were evaluated using the PP dataset. Safety assessment included statistical analysis of adverse events such as dizziness and falls, with the SS dataset used for safety assessment.

All statistical analyses were performed using SPSS 24.0 software. Two-tailed tests were used for statistical analysis, the primary outcome indicator is  $P < 0.025$  and the secondary outcome indicator is  $P < 0.05$  are considered statistically significant in comparison between groups. Continuous data were presented as means, standard deviations, or medians, and interquartile ranges depending on the normality of distribution. Categorical data were presented as frequencies (percentages). Normality tests were conducted for variable distributions, and independent sample t-tests were used for intergroup comparisons of normally distributed continuous data. Non-parametric tests were used for statistical analysis of non-normally distributed continuous data. Chi-square tests were used for comparisons of categorical variables, with the Fisher exact probability test used when necessary.

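### No planned sensitivity analysis lets unobserved outcomes differ from observed ones, so informative dropout goes untested, chiefly at the 12-week follow-up

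*Combined protocol and SAP*

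**What the plan says.** The Missing data section of the SAP sets the main approach: "The multiple imputation method will be preferred for analyzing the missing data". On the imputation model it says only this: "The patients' demographic characteristics were involved in the missing data model for multiple imputation", and "the number of multiple imputation will be set as 5". Treatment arm, baseline score and the score at the other visit are not mentioned. The section also asks for the percentage missing and for a look at missingness patterns. Its one named sensitivity analysis is complete-case: "the complete-case data should be reported in the manuscript as sensitivity analysis". The Data set section repeats this at the end of the per-protocol definition: "Prespecified sensitivity analyses were conducted using complete-case data".

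Data management and general analysis sets the analysis populations: "The primary outcome evaluation used the ITT dataset as the main dataset", with "the PP dataset for sensitivity analysis". Under Data set, per-protocol participants must, among other things, "have completed the treatment protocol", adhere well and have complete baseline values. Complete outcome data are not required.

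Footnote a to Table 1 (protocol, Study Design) provides for the T2 visit when a participant withdraws or is stopped early. T3 has no such provision. No delta-adjusted, tipping-point, reference-based, pattern-mixture or selection-model analysis appears in the protocol or SAP.

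**The concern.** A sensitivity analysis for missing data is useful when it varies the assumption that cannot be checked. Standard multiple imputation, and no other kind is described, treats missing outcomes as predictable from observed ones. Complete-case analysis leaves the missing outcomes out. The per-protocol set narrows the sample further, on completion and adherence. None of these deliberately asks what happens if people whose outcome was not seen fared worse than comparable people whose outcome was seen. Looking at missingness patterns cannot answer that either.

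The question is a live one here. The programme asks for 5 × 6 = 30 Tai Chi sessions and 30 rTMS sessions, followed by a later assessment, and the sample size already allows for 10% dropout. If leaving depends on poor response or discomfort and differs by arm, the trial could report consistent results across its analyses and call them robust without having examined this.

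**Working it through.** **Inputs.** From Sample size (Tai Chi reference): PSQI 11.26 (SD 1.52) against 12.48 (SD 2.59), alpha 0.05, power 0.80, 10% dropout, 49 per group raised to 55. From Data management and general analysis: two-sided tests, 0.025 for primary outcomes. Assumed: dropout rates other than 10%; an observed difference equal to the design difference; only active-arm imputed values shifted; where stated, a baseline–outcome correlation of 0.5.

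**1. The plan's own figure.** Difference = 12.48 − 11.26 = 1.22. SD = √((1.52² + 2.59²)/2) = 2.123. Standardized difference = 1.22/2.123 = 0.575. The noncentral t calculation gives 49 per group (power 0.804). Then 49/0.9 = 54.4, rounded up to 55, or 110 in total. The stated figure reproduces. It does not decide the point; it only supplies inputs.

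**2. Tipping point.** If a fraction f of the active arm is missing and those values are δ points worse than imputed, the difference falls by fδ. Significance is lost once 1.22 − fδ < c, where c = 2.241 × SE and SE = 2.123 × √(2/n observed per arm). So δ* = (1.22 − c)/f, computed here without rounding:

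| Missing per arm | Observed per arm | SE | c | δ* (PSQI points) |
|---|---|---|---|---|
| 3/55 (about 5%) | 52 | 0.416 | 0.933 | 5.25 |
| 5/55 (about 10%) | 50 | 0.425 | 0.952 | 2.95 |
| 8/55 (about 15%) | 47 | 0.438 | 0.982 | 1.64 |
| 11/55 (20%) | 44 | 0.453 | 1.015 | 1.03 |

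With t quantiles instead, the 10% and 20% values are about 2.8 and 0.94. Holding the SE at its full-sample value (2.123 × √(2/55) = 0.405, c = 0.920 with the t quantile) gives (1.22 − 0.920)/0.10 = 3.0 and (1.22 − 0.920)/0.20 = 1.5. The last figure is too lenient, because it ignores the information lost when 20% are missing.

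**3. A benchmark.** Suppose missing active participants keep none of the benefit, so δ = 1.22. At 5/55 missing, the difference is 1.22 − 0.0909 × 1.22 = 1.11, still above 0.952. At 20% it is 1.22 − 0.20 × 1.22 = 0.976, just below 1.015.

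**4. Effect of baseline adjustment.** The table is unadjusted. With a correlation of 0.5 the SE shrinks by √(1 − 0.5²) = 0.866. At 10%, c = 0.952 × 0.866 = 0.824 and δ* = (1.22 − 0.824)/0.0909 = 4.4. At 20%, c = 1.015 × 0.866 = 0.879 and δ* = (1.22 − 0.879)/0.20 = 1.7.

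**5. Does agreement reassure?** Simulation: 2,000 trials per scenario, 55 per arm, one visit, baseline-adjusted regression, correlation 0.5, 5 imputations, true effect about −1.22. In the informative scenario, active-arm participants with worse outcomes tend to go missing; in the control arm missingness is random. Mean estimates:

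| Scenario | Full data | Complete-case | MI: arm, baseline, demographic | MI: demographic only | MI with arm and baseline, +2 for missing active |
|---|---|---|---|---|---|
| Random, 10% | −1.21 | −1.21 | −1.21 | −1.08 | −0.99 |
| Informative, 10% | −1.23 | −1.49 | −1.48 | −1.39 | −1.27 |
| Random, 20% | −1.23 | −1.23 | −1.23 | −0.99 | −0.83 |
| Informative, 20% | −1.22 | −1.69 | −1.69 | −1.46 | −1.29 |

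Under informative dropout, complete-case and the fuller imputation agree with each other and both overstate the effect, by about 0.26 points (10%) and 0.47 points (20%). With demographics-only imputation the two differ, but by a similar amount whether dropout is random (0.13 and 0.24) or informative (0.10 and 0.23). In neither case does comparing the two reveal informative dropout.

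**The case against.** Several points on the other side stand.

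- A reader might infer that complete-case analysis rests on stronger assumptions than the imputation it accompanies. That is the usual ordering when the imputation model is rich, but this SAP names only demographics for the imputation, while the GEE adjusts for baseline. As described, complete-case may be the less biased of the two: under random dropout it is on target, and demographics-only imputation is pulled towards zero. If arm is left out, missing active participants are also drawn towards the pooled mean. That is a weakness of the imputation model and does not turn complete-case into a test of informative dropout.
- A reader might take the per-protocol analysis for a missing-data check. The SAP calls it a sensitivity analysis of the intervention effect on the primary outcomes, and its definition does not require complete outcomes.
- The T2 visit at withdrawal means that stopping treatment need not leave T2 missing.
- A reader might cite the 3.43-point difference in the rTMS reference study (11.45 − 8.02) to argue that a 3-point shift is plausible. That mixes two studies. With that study's SDs (2.53 and 6.14, pooled 4.70), significance needs about 2.03 points, and the tipping value at 10% missing is (3.43 − 2.03)/0.10, about 14 points on a 0–21 scale.
- Only 10% dropout is planned; 20% has no source in the documents. No passage contradicts another and no commitment is broken.

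What the objection does not supply is any planned analysis in which unobserved outcomes are allowed to depart from what the imputation predicts.

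**Conclusion.** The point holds in a limited form. The only missing-data sensitivity analysis named is complete-case, and per-protocol is a further restricted set. Agreement of either with the imputed result would not show that informative dropout is harmless. The exposure is chiefly at T3.

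The size is modest at the planned dropout. Under the inputs above, about a 3-point shift in missing active-arm participants is needed at 10%, more with baseline adjustment, and full loss of a 1.22-point benefit would not suffice. The result becomes fragile only if dropout is clearly higher: about 1 point at 20% unadjusted. These figures assume that the observed effect equals the design difference and that only active-arm values shift. Actual dropout is unknown, and the documents give no MoCA effect or SD from which to compute a parallel figure. This is a worthwhile addition to the plan; it does not invalidate the primary analysis.

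**What to change.** On the ITT set, for PSQI and MoCA at both T2 and T3:

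1. State the imputation model and include arm, baseline score and the other visit's score alongside demographics. The sensitivity analysis needs this base, since a penalty added to a demographics-only imputation would be hard to interpret.
2. Prespecify a delta-adjusted (tipping-point) analysis that worsens imputed active-arm values over a fixed grid, for example PSQI +1 to +4 and MoCA −1 to −4. Re-run the primary GEE at each step and report the shift at which the conclusion changes, or state that none on the grid changes it.
3. Keep complete-case as a supplementary analysis.

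The cost is a little more analysis work and no new data. The downside is that the result may look less robust than the present plan would show.

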### Data management and general analysis

A comparison of baseline characteristics of the selected subjects in the two groups was conducted to assess comparability. Intervention effect evaluation included determining

intervention effect indicators and comparing intervention effects between groups. The primary outcome evaluation used the ITT dataset as the main dataset for intervention effect evaluation and the PP dataset for sensitivity analysis. Secondary outcome indicators were evaluated using the PP dataset. Safety assessment included statistical analysis of adverse events such as dizziness and falls, with the SS dataset used for safety assessment.

All statistical analyses were performed using SPSS 24.0 software. Two-tailed tests were used for statistical analysis, the primary outcome indicator is  $P < 0.025$  and the secondary outcome indicator is  $P < 0.05$  are considered statistically significant in comparison between groups. Continuous data were presented as means, standard deviations, or medians, and interquartile ranges depending on the normality of distribution. Categorical data were presented as frequencies (percentages). Normality tests were conducted for variable distributions, and independent sample t-tests were used for intergroup comparisons of normally distributed continuous data. Non-parametric tests were used for statistical analysis of non-normally distributed continuous data. Chi-square tests were used for comparisons of categorical variables, with the Fisher exact probability test used when necessary.

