### **Primary Outcomes**

**Sleep quality assessment:** Use the internationally recognized Pittsburgh Sleep Quality Index (PSQI) to assess the sleep quality of the subjects in the past month. The PSQI scale consists of 19 self-assessment items, comprising 7 dimensions: sleep quality, sleep onset latency, sleep duration, sleep efficiency, sleep disturbances, use of sleep medication, and daytime dysfunction. Each dimension is scored on a scale of 0-3, with the cumulative score of all dimensions representing the total PSQI score, which ranges from 0 to 21. A higher score indicates poorer sleep quality.

**Global cognitive function:** The Montreal Cognitive Assessment (MoCA) (FuZhou Edition) was used to assess the Global cognitive function of patients. which includes 8 cognitive domains and 11 examination items covering visuospatial and executive functions, naming, memory, attention, language, abstraction, delayed recall, and orientation. The MoCA score ranges from 0 to 30, with higher scores indicating better overall cognitive function. If the education level is  $\leq 12$  years, an additional point is added to the total score, and a score of  $< 26$  indicates mild cognitive impairment (MCI).

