### **Analysis of secondary endpoints**

Statistical analysis of the secondary outcome indicators was performed using the PP dataset. The baseline measurements of the study subjects were adjusted using a generalized estimating equation model to compare the intervention effects in each group. At a single time point, the intergroup differences at baseline, 6-week postintervention, and during 12-week follow-up are compared using independent sample t-tests or Mann-Whitney U tests.

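### The secondary outcomes are analysed only in the per-protocol set, so their between-group tests are not protected by randomisation; ITT should be the main set, with PP as sensitivity

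*Combined protocol and SAP*

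**What the plan says.** The SAP assigns the secondary outcomes to one analysis set, and does so twice. Under Data management and general analysis: "Secondary outcome indicators were evaluated using the PP dataset". Under Analysis of secondary endpoints: "Statistical analysis of the secondary outcome indicators was performed using the PP dataset". Neither section, nor any other, names an ITT analysis of a secondary outcome.

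The primary outcomes are treated differently: "The primary outcome evaluation used the ITT dataset as the main dataset for intervention effect evaluation and the PP dataset for sensitivity analysis".

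The sets are defined in the SAP section Data set. ITT "refers to all participants who were randomized into different treatment groups, regardless of whether they completed the treatment as assigned or not". PP is limited to participants who meet the inclusion criteria, "do not meet the exclusion criteria, and have completed the treatment protocol". The section adds: "Each subject in the PP dataset is a valid case or sample with good adherence, no protocol violations, and complete baseline values for key indicators". It gives no numeric threshold for adherence.

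Three other provisions bear on the point:

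- Protocol, Table 1, footnote a: the T2 visit is also held for participants who withdraw or are terminated early. Every secondary outcome is scheduled at T2.
- SAP, Missing data: multiple imputation is preferred for missing data in the study generally, with complete-case analysis as sensitivity. Only demographic characteristics are named for the imputation model.
- SAP, Data management and general analysis: secondary outcomes are tested between groups, two-sided, at P < 0.05.

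**The concern.** Randomisation makes the two arms comparable as randomised. Whether a participant completes treatment, adheres well or violates the protocol is settled afterwards and can depend on tolerability, on perceived benefit or on how staff handle the participant. If the reasons for exclusion differ between arms, the retained groups are no longer comparable, and a difference can appear with no treatment effect or a real one can be distorted. In a superiority comparison, restricting to PP is not a conservative choice.

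At stake are the memory, executive-function and attention tests, the only objective sleep measure, and the sleepiness, mood and quality-of-life scales. Each is a between-group comparison with its own significance threshold, and the plan gives none of them an all-randomised analysis.

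**Working it through.** **1. What each set conditions on.**

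| | Primary (PSQI, MoCA) | Secondary (all eight) |
|---|---|---|
| Main set | ITT: all randomised | PP |
| Sensitivity set | PP | no alternative population named |
| Conditions on post-randomisation events? | Not in the main analysis | Yes, in the only analysis |

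A participant who stops early and attends T2 has secondary data but has not completed the treatment protocol, and so falls outside PP. Imputation does not repair this: it fills gaps among those analysed and cannot return someone removed from the set.

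**2. The plan's own sample size**, needed only for the number per arm. Inputs from Protocol, Sample size: PSQI 11.26 (SD 1.52) versus 12.48 (SD 2.59), alpha 0.05, power 0.80, 10% dropout.

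- Pooled SD = sqrt((1.52² + 2.59²)/2) = 2.123; d = 1.22/2.123 = 0.575.
- The two-sample t calculation gives 49 per group; 49/(1 − 0.10) = 54.4, rounded up to 55; total 110. The plan's figures reproduce.

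**3. Illustration of the bias.** The exclusion rates and gaps below are assumptions; the documents give neither. Let there be no true effect and an outcome SD of 1. A fraction p of each arm is excluded from PP. In the active arm the excluded have a mean g SD worse than the retained; in the sham arm exclusions are random.

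- The active-arm mean over all randomised is the retained mean minus p × g, so the PP comparison is shifted by b = p × g.
- Number per arm: n = 55 × (1 − p). Standard error: SE = sqrt(2/n).
- Type I error at nominal 0.05 = Φ(b/SE − 1.96) + Φ(−b/SE − 1.96).

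| p | n per arm | g (SD) | b (SD) | Type I error |
|---|---|---|---|---|
| 5% | 52.25 | 0.5 | 0.025 | 0.052 |
| 5% | 52.25 | 1.0 | 0.05 | 0.058 |
| 10% | 49.5 | 0.5 | 0.05 | 0.057 |
| 10% | 49.5 | 1.0 | 0.10 | 0.079 |
| 20% | 44 | 0.5 | 0.10 | 0.076 |
| 20% | 44 | 1.0 | 0.20 | 0.155 |

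**4. Extreme case at 10%.** If the excluded active participants are exactly the worst-responding tenth of a normal distribution and sham exclusions are random, the shift is φ(z)/(1 − p) = 0.1755/0.90 = 0.195 SD. At 5% the same formula gives 0.109 SD.

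**5. What drives the result.** The bias comes from a difference in selection between arms. If sham exclusions had the same gap g at the same rate p, the two shifts would cancel under no effect. If the excluded active participants were better rather than worse than those retained, the sign would reverse.

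**The case against.** The strongest defence is that the design limits differential exclusion. Both arms have the same Tai Chi and stimulation schedule, the sham coil looks identical, participants are meant to be unable to tell the coils apart, missed classes can be made up at home by video, and attendance above 90% is the target. The choice of set is prespecified and consistent, and the outcomes are secondary. This stands as a reason to expect modest bias. It does not exclude bias: Quality Control for Intervention Processes states that therapists knew which coil they were using, good adherence has no threshold, and nothing says whether home practice counts towards it.

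Several stronger readings are tempting but not supported:

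- *All cognitive results are affected.* They are not. Global cognition is a primary outcome ("The Montreal Cognitive Assessment (MoCA) (FuZhou Edition) was used to assess the Global cognitive function of patients") and is analysed in ITT. Only WMS-RC, Stroop and TMT-B among the cognitive tests are affected.
- *Secondary results cannot be set beside the primary ones.* They can, because the primary outcomes are also analysed in PP. The mismatch of populations is with the main primary analysis only.
- *Imputation is reserved for the primary outcomes.* The Missing data section has no such limit. What the secondary outcomes lack is the ITT set.
- *The bias favours active treatment.* Nothing in the documents fixes its direction.
- *The expected bias is 0.195 SD, about a third (0.195/0.575 = 34%) of the planning effect.* That figure is an extreme case. It uses the 10% dropout allowance as if it were the PP exclusion rate, and the 0.575 SD belongs to PSQI; no planning effect is stated for any secondary outcome. Nor is it the amount that ITT would remove: where the worst responders leave no data, imputation from demographics cannot recover them.

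**Conclusion.** The point holds on the text. Eight secondary outcomes have no all-randomised analysis, and their only set is selected on events after randomisation. The conclusion rests on the definitions, not on the illustration.

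The size and direction of any bias are unknown. Under the assumptions shown (5% to 20% excluded per arm, excluded active participants 0.5 to 1.0 SD worse, sham exclusions random, no true effect), bias is about 0.025 to 0.20 SD and type I error about 0.052 to 0.155 against a nominal 0.05. At the low end it is negligible; at the high end it would matter for any secondary claim.

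A reader might infer that the trial's conclusions are compromised. The documents do not support that: the PSQI and MoCA conclusions already rest on ITT with PP as sensitivity. This should be fixed before any secondary efficacy result is relied on, but it does not threaten the primary inference.

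**What to change.** Change the two sentences, under Data management and general analysis and under Analysis of secondary endpoints, so that the main analysis of every secondary outcome uses the ITT set with the planned baseline-adjusted GEE and multiple imputation. Keep PP as a sensitivity analysis, as for the primary outcomes. Include the T2 assessments of participants who withdrew. To make the PP analysis reproducible, state a numeric definition of good adherence and fix PP membership before group codes are released.

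The cost is small: the ITT set, the GEE model and imputation are already in the SAP, and no new data are needed. There are two downsides. ITT estimates may be slightly smaller than PP estimates. And imputation on demographics alone will not fully correct dropout that depends on outcome, particularly at T3, because the footnote that secures a visit after withdrawal covers T2 only.

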### **Secondary outcomes**

#### **Memory function assessment:**

**Wechsler Memory Scale (WMS-RC):** Widely used for assessing memory function, the WMS-RC reflects the overall level of memory function. WMS-R mainly tests the functions of immediate memory, working memory, and long-term memory. The final score of WMS-RC is calculated as MQ, and a higher MQ score indicates better memory.

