#### **Executive function assessment:**

**Stroop test Victoria version:** The classic Stroop test includes interference and control tasks. The Victoria Stroop Test (VST) uses three conditions, including naming the color of dots, the color of neutral words, and the color of colored words printed in incongruent colors. Participants are required to quickly identify the color of a series of words. The tester records the "total time taken".

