#### **Attention**

**Trial Making Test Part B (TMT-B):** TMT-B consists of numbers 1-25 in circles and squares, requiring participants to connect the numbers in ascending order as quickly as possible while alternating between the two shapes. The evaluator records the time taken to complete the task, with shorter completion times indicating better performance.

**The objective sleep quality:** The Wrist actigraphy, which integrates a three-axis accelerometer and an optical heart rate sensor, was used to record objective sleep quality data

. The subjects wore the device on their non-dominant wrist before going to bed. The built-in three-axis accelerometer recorded the acceleration signals of the wrist and converted them into digital signals for storage. After connecting the finger cuff with the optical heart rate sensor to the body movement recorder, the photoelectric pulse wave recording method was used to collect pulse wave signals by emitting infrared light to the skin. The sleep status of the subjects was monitored for seven consecutive nights at baseline and after treatment. Objective sleep data would be extracted after the participants returned the wrist-worn body movement recorder, and subsequent data analysis would be conducted. This included sleep efficiency (total sleep time / total time in bed x 100%), time of arousal after falling asleep, number of arousals per night, sleep latency, total sleep time, and average arousal time per arousal.

**Epworth Sleepiness Scale (ESS):** This scale contains eight scenarios describing daily life situations. Subjects are required to evaluate their tendency towards sleepiness based on these scenarios. Each scenario has a score ranging from 0 to 3, indicating the degree of sleepiness tendency in the corresponding situation. The total score ranges from 0 to 24. A score greater than 6 suggests drowsiness, greater than 11 indicates excessive drowsiness, and greater than 16 suggests dangerous drowsiness.

**Hamilton Anxiety Rating Scale (HAMA):** This scale is used to assess patients' anxiety symptoms over the past week, including anxiety level, tension, fear, and other manifestations. HAMA consists of 14 items, with scores ranging from 0 to 4, to assess the severity of anxiety symptoms. The higher the total score, the more severe the patient's anxiety symptoms.

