### Covariates and subgroup analysis

If there are statistically significant differences in the inter-group comparison of baseline indicators, covariates should be included in the analysis after intervention for correction. Use Generalized Estimating Equation (GEE) model to analyze primary and secondary outcome measurements. While including baseline measurements and IPAQ as covariates in the analysis. In addition, subgroup analysis will be performed by sex, age, education, BMI at baseline, GDS-15. The subgroup analysis will be carried out as exploratory.

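### At least 13 secondary measures are each called significant at two-sided P < 0.05 with no order, gate, correction or supportive label; with 20 tests and moderate assumed correlation, a false benefit on at least one arises in roughly 2 to 3 of 10 null trials.

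*Combined protocol and SAP*

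**What the plan says.** Three groups of analyses are treated differently in the SAP.

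- **Primary outcomes (PSQI and MoCA).** Under Data management and general analysis, significance requires P below 0.025.
- **Secondary outcomes.** The same sentence continues: "the secondary outcome indicator is $P < 0.05$ are considered statistically significant in comparison between groups". All tests are two-sided ("Two-tailed tests were used for statistical analysis"). Analysis of secondary endpoints plans a GEE model adjusted for baseline and then adds: "At a single time point, the intergroup differences at baseline, 6-week postintervention, and during 12-week follow-up are compared using independent sample t-tests or Mann-Whitney U". It does not say whether the GEE or the time-point test settles a claim.
- **Subgroups.** Under Covariates and subgroup analysis: "The subgroup analysis will be carried out as exploratory".

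The secondary outcomes are defined in the protocol under Secondary outcomes: WMS-RC, Stroop, TMT-B, ESS, HAMA, HAMD, SF-36 and actigraphy. Actigraphy supplies sleep efficiency plus five more parameters: "time of arousal after falling asleep, number of arousals per night, sleep latency, total sleep time, and average arousal time per arousal". Table 1 schedules the seven scales and tests at T2 and T3, and actigraphy at baseline and T2 only.

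**The concern.** The primary threshold equals 0.05/2, which fits two primary outcomes, and the subgroups carry an exploratory label. The secondary outcomes get neither treatment. They get a rule that attaches the words statistically significant to any comparison below 0.05, whatever happened on PSQI and MoCA.

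The measures cover memory, executive function, attention, objective sleep, sleepiness, mood and quality of life. With that many chances, an isolated P of 0.04 on one of them is not surprising when active rTMS adds nothing to Tai Chi Chuan. Under the plan it would still count as a significant difference between groups. At stake is what the trial may claim from its secondary outcomes, not the primary result.

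**Working it through.** **The plan's own figure.** The SAP states no error rate for the secondary outcomes as a set. The related figure is the primary threshold: 0.05 / 2 = 0.025. For two independent tests, 1 − 0.975² = 0.049, so the two primary outcomes together stay within 0.05.

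**Counting the secondary tests.**

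- Seven scales or tests, each taken as one score: WMS-RC ("The final score of WMS-RC is calculated as MQ"), Stroop, TMT-B, ESS, HAMA, HAMD and SF-36.
- Six actigraphy parameters.
- Measures: 7 + 6 = 13.
- Post-baseline measure-by-visit comparisons: 7 × 2 + 6 × 1 = 20.

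Thirteen is a minimum: "The Victoria Stroop Test (VST) uses three conditions", and the protocol does not say whether SF-36 is one score or several. The baseline comparisons are left out.

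**Formula.** The correlation between test statistics is not in the documents. I assume equicorrelated normal statistics with correlation r from 0 to 0.8, and no true effect on any measure. Let c = 1.96, k be the number of tests and U a standard normal variable.

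- Either direction: 1 − E[{Φ((c − √r·U)/√(1−r)) − Φ((−c − √r·U)/√(1−r))}^k]
- Favouring active rTMS: 1 − E[Φ((c − √r·U)/√(1−r))^k]

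At r = 0 these reduce to 1 − 0.95^k and 1 − 0.975^k. For k = 20 that is 0.642 and 0.397; for k = 13 it is 0.487 and 0.280.

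**Chance of at least one false significant result** (numerical integration):

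| Assumed r | 20 tests, either direction | 20 tests, favouring rTMS | 13 tests, either direction | 13 tests, favouring rTMS |
|---|---|---|---|---|
| 0 | 0.642 | 0.397 | 0.487 | 0.280 |
| 0.3 | 0.540 | 0.280 | 0.418 | 0.214 |
| 0.5 | 0.419 | 0.210 | 0.334 | 0.167 |
| 0.7 | 0.290 | 0.145 | 0.241 | 0.120 |
| 0.8 | 0.224 | 0.112 | 0.192 | 0.096 |

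Simulation with 200,000 null sets agrees to within 0.003; for example, 20 tests at 0.8 in either direction give 0.225.

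**Sensitivity to the visit structure.** Equal correlation ignores that seven measures repeat at two visits. With a separate between-visit correlation of 0 to 0.7, the 20-test chance of a false benefit is 0.28 to 0.32 at between-measure correlation 0.3, and 0.22 to 0.26 at 0.5. The conclusion does not change.

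**Expected number of false results.** This does not depend on correlation. For 20 tests: 20 × 0.05 = 1.0 in either direction and 20 × 0.025 = 0.5 favouring rTMS. For 13 tests: 0.65 and 0.325.

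**The case against.** Unadjusted secondary testing is common, and the SAP does rank the primary outcomes above the secondary ones: a stricter threshold, and ITT as the main dataset rather than PP alone. It never calls the secondary outcomes confirmatory and never promises a 5% error rate across them; 0.05 is a per-comparison threshold. All of that stands. A reader might infer that the plan breaks a family-wise guarantee, but it gives none to break. What is missing is any order or label within the secondary set, and a stated rule for significance is not a substitute for one.

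A reader might also infer that a false secondary benefit is expected in about 4 of 10 null trials. The documents do not support that as the central figure. At correlation 0.5, 0.42 is the chance of a false result in either direction, including results that favour sham; in the direction of benefit it is 0.21. The benefit figure reaches 0.40 only with 20 independent tests. Independence is implausible here: the same patients supply every measure, seven measures are repeated, and six parameters come from the same actigraphy recordings.

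The count of 20 also depends on the time-point tests deciding. If one GEE test per measure decides, 13 is the right count.

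**Conclusion.** The concern holds as a labelling gap with a material error rate. For 20 tests, a false secondary benefit has a chance of roughly 2 to 3 in 10 at moderate correlation (0.28 at 0.3, 0.21 at 0.5), within a range of 0.40 to 0.11 for correlations from 0 to 0.8. For 13 tests it is 0.17 at 0.5, within 0.28 to 0.10. In either direction the ranges are 0.64 to 0.22 and 0.49 to 0.19. These figures assume no effect on any measure and equal correlation, and the correlation is not a figure from the documents.

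Even the lowest case is about four times the single-test level: 0.19 against 0.05 in either direction, or 0.10 against 0.025 for benefit. The sponsor should act. The primary threshold and primary conclusions are untouched.

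**What to change.** In the SAP, Data management and general analysis, replace the 0.05 significance rule for secondary outcomes with:

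> Secondary outcomes are supportive; they are reported as between-group differences with 95% confidence intervals, not adjusted for multiplicity, and are not used as confirmatory evidence of efficacy.

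This works whichever test decides, so it does not depend on settling the count. It costs one sentence and needs no new data or patients. The downside is that an isolated secondary result with P < 0.05 can no longer be presented as a confirmed finding. If the analyses have already been run, the same label can be applied in reporting.

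I do not propose a gated list of secondary claims. It would first need a decision on whether one or both primary outcomes must succeed and how much alpha then passes down, and the order could not be chosen after seeing the data.
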